opioids 24 – 72 hours prior to induction. If given too early, buprenorphine can rapidly precipitate an intense opioid withdrawal. Because of concerns about this risk, inductions have often occurred in the primary care clinic with monitoring from the clinic staff (“observed” or office-based induction). Timing the last use of opioids such that patients arrive during available office hours for induction while in withdrawal is challenging. Further, office induction is a resource intensive activity requiring space, provider and staff time, and patient effort. Based on our previous work (IT MATTTTRs), office-based induction might require one to three hours of patient time in the office, two to four staff interactions, and one to three prescriber interactions. Other care providers, including behavior health, peer counselors, and ancillary staff may have additional interactions with the patient. Busy primary care practices, rural health centers, Federally Qualified Health Centers, and other safety net clinics must balance access to onsite care for many patients with the needs of an individual patient with OUD. Some practices are reluctant to dedicate this amount of resource for one patient encounter. Although resource intense, these same office-based resources might also create a positive cumulative benefit for patients not available in-home inductions, including enhanced patient-provider-practice interaction and support for patient behavioral factors (motivation, planning, and action control) known to affect long-term adherence to treatment

Home (or “unobserved”) induction is an alternative strategy that poses fewer practice challenges and allows patients to begin buprenorphine therapy according to their schedule. For home induction, patients can stop opioids at any time and start buprenorphine when they reach the appropriate level of withdrawal. Stigma associated with OUD and difficulty with transportation may present other barriers to starting MAT at the clinic. Some patients may prefer undergoing MAT induction in the relative comfort of their own home. However, while potentially more convenient, some patients lack social supports and relationships and the cognitive ability to set goals and follow through on plans (low executive function) often necessary for successful MAT induction and treatment.

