### Patient Data

#### *Practice Tracker*

Patient-level data will include the use a Practice Participant Tracker by participating practices to document participant information and clinical care activities. The Tracker will be a binder organized with numbered tabs for each participating patient or electronic Excel file. A spreadsheet for each patient will include a virtual 300-day timeline from initial identification through final data collection. This Tracker will be used to record patient enrollment, completion

of patient MAT education, induction type, induction Day 1 date, prescriptions and refills, urine buprenorphine and urine opioid test results, contacts with patients (when and whether these be via phone, e-mail, or in person), and continuation or discontinuation of treatment. Practices may record information either on paper or electronically with periodic transmission to the central data management team electronically or via secure fax. Summary notes will be recorded from the monthly check-in calls with practices. A template copy of the Practice Participant Tracker will be submitted to COMIRB for review and approval prior to use. Practices will receive \$200 for each patient enrolled from their practice (up to 12) and \$35 per patient per month for up to nine months of monitoring maintaining follow-up with each patient in their Practice Participant Trackers, paid at the end of the data collection phase.

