### Surveys

Patient participants will be asked to complete questionnaires and assessments (surveys) pertaining to social determine of health and quality of life. Surveys will be administered at baseline, 30 days, 90 days, and 270 days. Participants will receive a \$50 gift card (e.g., Amazon, Walmart) per time (baseline, 30 days, 90 days, and 279 days), totaling up to \$200 in gift cards. Respondents will have the option the complete their surveys online using REDCap or on hard copy. With hard copies, packets will include a postage-paid envelope to mail completed surveys back to the research team at the University of Colorado. Final selection of these questionnaires and assessment will be made and submitted to COMIRB for review and approval prior to use.

A summary of the study measures and potential data collection tools is shown in Table 1.

Table 1 Outcomes, Measures, and Potential Data Collection Tools

| Outcome                                                                                                                                                   | Measure                                                                                                                                                                                                                                                                        | Data Collection Tool(s)                                                                                                                                                                                                                                                                                                                                                                   |

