|-----------------------------------------------------------------------------------------------------------------------------------------------------------|--------------------------------------------------------------------------------------------------------------------------------------------------------------------------------------------------------------------------------------------------------------------------------|-------------------------------------------------------------------------------------------------------------------------------------------------------------------------------------------------------------------------------------------------------------------------------------------------------------------------------------------------------------------------------------------|
| Primary Outcomes                                                                                                                                   | Timing of data collection indicated by *, **, †, ‡, §, ¶                                                                                                                                                                                                                |                                                                                                                                                                                                                                                                                                                                                                                           |
| Number of days patient took buprenorphine between Day 1 and Day 270†                                                                                      | 
 
▪ Prescription refills†
 
▪ Patient self-report of number of days buprenorphine taken†
 
                                                                                                                                | 
 
▪ Practice Participant Tracker
 
                                                                                                                                                                                                                                                                                                          |

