#### *Specific Tests and Analysis Plans for Outcomes, by Hypotheses*

***H1: Patients using observed (office-based) MAT induction will have a greater number of days of buprenorphine treatment than patients using unobserved (home) MAT induction at nine-month follow-up.***

The outcomes for these analyses will be the total number of days of buprenorphine treatment during the nine-month follow-up period. The structure of the data is hierarchical (patients nested within practices). Intervention is an indicator variable: 0= home-based induction, 1= office-based induction. Covariates will be included in all models but are not shown here for ease of understanding. Since we anticipate the distribution will be over-dispersed, we will not use a Poisson model. Instead, we will first examine the distribution of the outcome data (counts and/or proportions) and explore alternatives such as negative binomial (or possibly beta binomial on proportions), using model diagnostics and goodness of fit measures to select the best approach. For the negative binomial model, modeling counts ( $Y_{ij}$ ) we have

$$\text{Log}(Y_{ij}) = \gamma_{00} + \gamma_{01}(\text{intervention}) + \gamma_{02}(X_{i.}) + u_{0j}$$

where  $\gamma_{00}$  represents the mean (in terms of logs) for home-based induction;  $\gamma_{01}$  represents the difference between means for the office-based vs home induction group;  $\gamma_{02}$  is the effect of patient level covariates on log counts, and  $U_{0j}$  is a practice random effect. Thus, the intervention effect of office-based vs home induction can be tested as  $H_0: \gamma_{01}=0$  vs  $H_1: \gamma_{01}\neq 0$ .

***H2: Patients using office-based MAT induction will be more likely to take buprenorphine on  $\geq 80\%$  of the days between day 1 and day 270 than patients using home MAT induction.***

The outcome for this analysis will be buprenorphine use on  $\geq 80\%$  of days (yes/no). We will use mixed effects logistic regression models (generalized linear mixed models with logit link) to analyze the data. The model will be similar to that shown above, with a random effect for practice and patient level covariates, along with a fixed effect for intervention group.

***H3: Patients using office-based MAT induction will report greater improvement in quality of life, social determinants of health and social functioning over a nine-month follow-up period than patients using home induction.***

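### The H1 and H2 outcomes count buprenorphine days from any source, but the only tool named for them is the enrolling practice's Tracker, so days obtained elsewhere after a patient leaves may be missed

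*Protocol*

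**What the plan says.** **Outcomes.** The analysis plan by hypothesis (section IV.F) takes for H1 the "total number of days of buprenorphine treatment during the nine-month follow-up period". For H2 it states "The outcome for this analysis will be buprenorphine use on" at least 80% of days, yes or no. The matching H1 row of Table 1 (section IV.D) reads "Number of days patient took buprenorphine between Day 1 and Day 270". None of these wordings refers to who prescribed the drug.

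**Measures and tool.** The H1 row lists two measures, "Prescription refills" and "Patient self-report of number of days buprenorphine taken". The H2 row lists prescriptions with refills, the same self-report, and urine buprenorphine tests. In both rows the tool column names only the Practice Participant Tracker.

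**The Tracker.** Under the Practice Tracker heading, participating practices keep this record. Its contents include "prescriptions and refills, urine buprenorphine and urine opioid test results, contacts with patients", and an item on whether treatment goes on or has stopped. Self-reported days are not listed, nor is a category for a patient who moves to another prescriber. Drop-out information also comes from the practice, at monthly check-ins.

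**Central contact with patients.** The research team surveys patients at baseline and at 30, 90 and 270 days. The Surveys section describes these questionnaires as "pertaining to social determine of health and quality of life". Two alternate contacts per patient are held for tracing.

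**Dropout.** The Sample Size and Power section says that dropout leaves some outcomes untouched, without naming them. It sizes treatment retention on 500 per arm and outcomes such as quality of life on 400.

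**The concern.** A patient can leave the enrolling practice and go on taking buprenorphine from another clinic. By the stated outcome those days count. By the stated tool they may never be seen: the practice would write no further refills, obtain no urine sample, and have no listed field for what the patient says. The protocol names no pharmacy, claims, prescription-monitoring or outside-prescriber source.

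An analysis plan can choose how to score such a patient, but it cannot recover days that nobody recorded. If the days are scored as untreated, the outcome is misclassified; if they are set to missing, information is lost. Either way the outcome depends on the patient staying with the practice, which sits badly with the statement that some outcomes escape dropout and with sizing retention on the full 500 per arm. Loss that is equal in both arms dilutes a true effect. Loss that differs by arm biases the comparison, and randomization does not protect against a difference in ascertainment that arises after it.

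**Working it through.** **Inputs from the protocol (section IV.F).** 500 patients per arm; 45% vs 54% on the dichotomous retention outcome; two-sided alpha 0.05; stated power 81%. Eighty per cent of 270 days is 0.80 × 270 = 216 days.

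**Assumed input.** Let t be the share of true successes (patients who really took buprenorphine on at least 216 days) who are recorded as failures because their later days came from elsewhere. The protocol gives no value for t and does not say that such patients are scored as failures. The figures below hold only if they are.

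**Step 1: reproduce the plan's power.** For the pooled z test,

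power = Φ[(|p2 − p1| − 1.96·s0)/s1], with s0 = √(2p̄(1 − p̄)/n), s1 = √([p1(1 − p1) + p2(1 − p2)]/n).

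With p1 = 0.45, p2 = 0.54, p̄ = 0.495, n = 500: s0 = 0.0316, s1 = 0.0315, and (0.090 − 0.0620)/0.0315 = 0.89. Power is 81.3%, which agrees with the stated 81%.

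**Step 2: equal loss in both arms.** The observed rate is p(1 − t).

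| t | Home | Office | Difference (points) | Power |
|---|---|---|---|---|
| 0 | 45.0% | 54.0% | 9.0 | 81.3% |
| 5% | 42.75% | 51.3% | 8.55 | 77.4% |
| 10% | 40.5% | 48.6% | 8.1 | 73.2% |
| 20% | 36.0% | 43.2% | 7.2 | 64.4% |

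**Step 3: unequal loss, no true effect (both arms 45%).** The spurious difference is 0.45 × (t home − t office). Rejection is counted in both tails.

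- 10% home, 5% office: 0.45 × 0.05 = 2.25 points; false rejection 11%.
- 15% home, 5% office: 0.45 × 0.10 = 4.5 points; false rejection about 31%.

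**Step 4: unequal loss the other way, true 9-point effect.** With 5% home and 15% office the observed rates are 0.45 × 0.95 = 42.75% and 0.54 × 0.85 = 45.9%. The difference is 3.15 points and power is 17%. The sign of any bias therefore depends on which arm loses more days, and the protocol does not say.

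**The case against.** The best reply is that self-report is already a measure in both buprenorphine rows, that a patient's count of days taken is not tied to one prescriber, and that H2 also has urine tests. There are signs that patients may be asked directly. The Consent and Tracking Procedures sections warn that patients may feel uneasy about questions on buprenorphine prescriptions. The neighbouring illicit-opioid row carries the timing mark used for the patient surveys, although its tool cell also names the Tracker. The timing mark on the self-report line has no key in the text as extracted; even if it means 30, 90 and 270 days, the tool cell still says Tracker. The survey description does not exclude other topics, and Table 1 assigns substance use, executive function and other items to surveys. The tools are called potential, the Tracker template was still to be submitted, and practices are paid to keep up follow-up, so some transfers would come to light.

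Much of this stands. Self-report might cover the gap, but the protocol gives it no stated route from a patient who has left. Urine results do not help, because they are a Tracker item.

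Three stronger readings are not supported:

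- A reader might infer that every day after transfer is scored as untreated. No section says so, and a scoring rule may properly sit in an SAP that is not shown.
- A reader might infer a built-in bias towards office induction from the expected "enhanced patient-provider-practice interaction and support for patient behavioral factors" in section III. That sentence is worded as a possibility and describes a route to real adherence. It says nothing about transfer.
- A reader might take a 5-point gap in transfer as a 5-point false difference on H2, more than half of the 9-point design difference. That requires every transferring patient to be a true success; at a 45% success rate the figure is 2.25 points.

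**Conclusion.** The point holds as a mismatch between outcome and instrument. H1 and H2 concern buprenorphine taken from any source, while the one named tool is held by the enrolling practice, does not list the self-report it is meant to carry, and cannot tell transfer from discontinuation. Days obtained elsewhere may be missed, as untreated or as missing. This goes beyond detail left to an SAP, because it concerns what is collected.

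The size is unknown. As illustration under assumed rates, and only if missed days are scored as untreated, an equal 10% loss of true successes lowers power from 81% to about 73%, and a 10% vs 5% loss yields a spurious 2.3 points with about 11% false rejection. A difference between arms is possible in either direction, but the protocol neither states nor quantifies one. The documents do not show that H1 and H2 measure attachment to the practice instead of treatment.

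**What to change.** 1. Collect the self-report that Table 1 already lists directly from patients, in both arms, in the existing central surveys at 30, 90 and 270 days. Ask whether buprenorphine came from any other prescriber or facility since the last survey, and on how many days it was taken from any source.
2. In the two buprenorphine rows of Table 1, name the patient survey as a second tool and define days as buprenorphine from any source.
3. Add a Tracker field that records transfer to another prescriber separately from discontinuation.
4. Report days documented by the enrolling practice alone as a sensitivity result.
5. State which outcomes the dropout sentence in Sample Size and Power refers to, and whether the buprenorphine outcomes are among them.

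The cost is two survey items, one Tracker field and some wording, in instruments the protocol describes as not yet final. The downside is that days after transfer rest on self-report, which Table 1 already accepts. The last recall interval would be 270 − 90 = 180 days, and survey non-response will leave some days missing. The change is needed before data collection, since the lost days cannot be rebuilt reliably afterwards.

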### Contact Information

Contact information for patient participants, including name, address, phone numbers and email address, will be obtained in order to remind participants to complete scheduled surveys and to send participants their gift cards each time they complete surveys and assessments. Alternate contact information will be obtained for two other people, family members not living with the participant or close contacts, who may be knowledgeable about the participant in the event that the participant cannot be contacted for subsequent longitudinal follow-up. Alternate contact information will include name, address, phone numbers and email addresses. All contact information will be stored securely in a database separate from that developed for the clinical and survey data and accessible only to the research team responsible for tracking patient participant payments (gift cards).

### Tracking Procedures

No names will appear on the surveys or Practice Participant Tracker data. Practice member surveys will include a unique ID linked to the practice only. Each patient participant will be assigned a unique ID by the research team. The unique ID keys will be stored separately from research data. We will use REDCap to send unique survey links to participants completing their surveys online. Hard copies of surveys will include the appropriate unique ID (practice-level for practice members and patient-level for participating patients). Survey data from written surveys will be entered into REDCap by a project team member. Hard copies will be locked in a secure filing cabinet in a locked office space in the Department of Family Medicine.

The unique patient participant ID will be used by practices to transmit de-identified data from the Practice Participant Tracker to the study team.

This project poses minimal risk to study participants. Participation is voluntary. Patient participants may be uncomfortable answering questions about buprenorphine prescription or illicit opioid use and other aspects of their lives. Participants can refuse to answer any questions

they want. Consent will be required. Key informant interview participants can determine the information they share during their interviews.

#### **E. Potential Scientific Problems:**

This is a comparative effectiveness research study, randomized at the patient level, to compare short-term stabilization and long-term maintenance treatment outcomes of home MAT induction to office MAT induction for patients suffering from OUD and opioid dependence.

#### **F. Data Analysis Plan:**

##### *Sample Size and Power:*

We aim to recruit 100 practices, enroll 1200 patients to reach a goal of 1000 patients receiving MAT induction (allowing for attrition prior to MAT induction), and randomize patients evenly to each study arm. For some outcomes (e.g., quality of life), we allow for ~20% attrition (leaving 800 patients total, 400 per arm). Some outcomes will not be affected by patient dropout, so we give a range of sample size estimates. With patient-level randomization, the impact of clustering will be minimal and is not considered here. For the dichotomous outcome of treatment retention, a sample size of 500 patients per arm will provide 81% power to detect a 9% difference in long-term treatment between study arms with  $\alpha=.05$  (e.g., 45% vs 54%). For continuous outcomes (e.g., quality of life, % of days taking buprenorphine out of 270 days), a sample size of 400 to 500 patients per arm will provide 81% power to detect an .18 to .20 SD difference (small) between study arms with  $\alpha=.05$ .

